### Evaluation of results

The primary outcome measure will be the mean blood pressure (MBP), and the secondary outcome measures will be the systolic and diastolic BP, HR and pulse pressure (PP). All of these will be measured over 24-h periods with a clinically-validated ABPM device, Watch BP 03. The research nurses will fit this ABPM device on patients and remove it after the 24-h measurement period, having first measured the patient’s BP with a validated OMRON M6 blood pressure monitor twice, or three times if the difference between the first two measurements is >5 mmHg. After that, they will give patients a notebook to record their activity, exercise and meals times as well as the time they go to bed and wake up during the 24 h of monitoring.

The systolic and diastolic BP as well as the HR will be measured every 20 min between 07:00 and 23:00 and every 30 min between 23:00 and 07:00. Monitoring will not be considered valid if >30% of the data are missing or if there is no data for a period >2 h. It will also not be considered valid if the patient has an irregular sleep-wake rhythm, with resting times >12 h or <6 h per night, during the monitoring period [17]. We will define the daytime BP as the mean of the measurements collected between 09:00 and 21:00 and the night-time BP as the mean of the measurements taken between 0:00 and 06:00, as this is the timetable that most closely matches the habits of most of our patients.

In addition, we will calculate the night/day ratio of the BP and classify patients according to this value ratio : >1, riser; >0.9 and ≤ l, non-dipper; >0.8 and ≤ 0.9 dipper; and ≤ 0.8, extreme dipper.

### Adverse effects

At each appointment with the patients, the nurse, as well as providing the medication for the following period and assessing treatment adherence, will ask the patient to record any AEs detected during the study period. These AEs will also be recorded by the nurse in the dedicated database, establishing their severity and assessing the causality with respect to the drug under study. Further, there will be an independent committee who will monitor the safety of the drug under study, by reviewing any AEs that occur during the entire study period.

In the event of a serious adverse reaction (SAR) or a suspected unexpected serious adverse reaction (SUSAR), it will not be necessary to break the blind nature of the study since the medical actions taken will be the same for all patients, independent of the knowledge of group allocation, since all the patients are taking the same active ingredient and the placebo. The only difference is time of day they are taking the drug. All the current regulations will, in any case, be complied with at all times and in the event of any of the aforementioned types of reaction, the relevant health authorities will be notified within 24 h of them being reported.

### Data quality and management

The coordination, control of quality of processes related to the study, data management and quality assurance will be the responsibility of the PCRUB. The patients will be randomly selected and the reasons for any being excluded will be recorded in their medical records and revised by the trial monitor. Changes in the BP of participants will be assessed by 24-h ABPM, coordinated by nurses trained in the technique, who will be blind to the assignment of patients to the comparison groups, under the supervision of the research team. Moreover, various measures will be taken to guarantee the quality and validity of the data collected in the study including:

•A EDC system will be created for recording data and steps taken to minimise errors in data recording and later processing of the data, such as double-data entry, follow-up of missing data, and automatic transfer of the ABPM data from the device to the EDC system, among others

•Documentation will be completed to ensure the traceability of the drug under study over the entire study period

•Inspections will be made to check that the study is being carried out in accordance with good clinical practices and the established protocol

### Sample size

A sample size of 258 patients, with 129 in each group, will provide a statistical power >80% for detecting as significant (*P*< 0.05) a difference of 2.5 mmHg between the mean arterial pressure with bedtime and daytime administration, using a two-tailed Student’s t-test (standard deviation obtained from previous studies, with similar populations to that of our project and estimated to be 8 mmHg) [4].

A reduction of 5 mmHg in arterial pressure is considered to be clinically significant at the individual level, since it is associated with a decrease of 12.5% in the risk of cardiovascular events and of 16.7% in the risk of acute cerebrovascular accidents [7]. We expect that with bedtime administration at least 50% of patients will achieve this level of reduction in BP, and that there will be no changes during day-time administration. Under this assumption, the mean difference between the two groups would be at least 2.5 mm/Hg.

These calculations are based on the formula for calculating sample sizes in cross-over clinical trials developed by Donner (1984) [18]. It has been assumed that around 5% of the BP measurements will not be valid, that around 15% will be lost to follow-up and that the intra-subject correlation will be 0.5.

### Analysis

First, an assessment will be made of the potential carry over effect of the treatment from the first period to baseline levels before the second period. The analysis will be carried out on an intention-to-treat basis, comparing the mean blood pressure at the end of the period of bedtime intake with that observed after the daytime intake, adjusting for the baseline blood pressure at the start of each period in all patients which at least have received one dose of treatment. Moreover, we will perform a per protocol analysis with only the patients have not change in their treatment within the 5-month period of the trial and have not been withdrawn. The effect attributable to bedtime intake will be estimated in terms of the difference in mean blood pressure between the two periods and the 95% confidence interval will be calculated using mixed-effect models analysis of covariance for repeated measures of blood pressure taken in each subject at the end of each of the periods. These models will include the patient as a random effect (intercept), to take into account the correlation between the two measurements in the same individual in each period. As well as adjusting for the baseline levels, we will adjust for potential confounding or modifying variables: changes in medication, period or sequence, age, sex, unhealthy habits as to be smoker or no smoker, risk factors as to be dipper or non-dipper comorbidity as diagnosis of dyslipemia, diabetes, stroke, peripheric arteriophaty or myocardial infarction and month of the year when the study is started. We will assess, by means of tests of interaction, the absence of a modifying effect of bedtime intake as a function of the period when patients took the ASA at this time.

A stratified analysis will be undertaken considering two groups, dippers and non-dippers, assuming that the prevalence of non-dippers in this population is 40%.

In the mixed-effect analysis, all the data available from each of the subjects included in the study will be considered, regardless of whether there is missing data. Values of missing data will not be imputed, except in the case of the baseline values for the second period, in which case they will be assigned the same value as the baseline measurements at the start of the study. It has been shown that this is more robust than other approaches to dealing with missing data.

All this analysis will be carried out using the SAS statistical package.

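### A single coefficient for the period-specific baseline would probably cost precision in the primary model, month of study start cannot adjust for season within a patient, and the model does not commit to a period term

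*Protocol article*

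**What the plan says.** The Analysis section of the protocol article takes blood pressure at the end of each period as the outcome and fits a mixed-effects analysis of covariance, "adjusting for the baseline blood pressure at the start of each period in all patients". On the correlation structure it says: "These models will include the patient as a random effect (intercept), to take into account the correlation between the two measurements". The further adjustment variables include "changes in medication, period or sequence", several patient characteristics, and "month of the year when the study is started". The section does not say whether the baseline has one coefficient or separate within-patient and between-patient coefficients.

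The Sample size section states "A sample size of 258 patients, with 129 in each group", which "will provide a statistical power >80% for detecting as significant (*P*< 0.05) a difference of 2.5 mmHg", "using a two-tailed" t-test, with the standard deviation "estimated to be 8 mmHg". It gives a single intra-subject correlation of 0.5 and allows for 5% invalid measurements and 15% loss to follow-up. The Study design section places the ABPMs at baseline and at 2, 3 and 5 months.

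**The concern.** In a two-period cross-over the treatment effect is estimated from the difference between a patient's two outcomes. A baseline measured at the start of each period varies both between and within patients. If it has one coefficient, a random-intercept model estimates that coefficient as a compromise between two slopes: a steep between-patient slope (patients with high pressure stay high) and a within-patient slope that may be close to zero. The compromise slope is then applied to the within-patient baseline difference. If that difference predicts little of the outcome difference, the adjustment adds noise to the contrast it was meant to sharpen. It also lets any residual bedtime effect in the second baseline into the estimate.

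The season and period terms raise a related question: does each vary within a patient, where the treatment comparison is made? Month of start does not vary within a patient, and neither does sequence. What is at stake is the width of the primary confidence interval.

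**Working it through.** **Inputs.** From Sample size: SD 8, correlation 0.5, target difference 2.5, two-sided 0.05, 258 patients, losses of 5% and 15%. Completers: 258 x 0.95 x 0.85 = 208. From Study design: ABPMs at months 0, 2, 3 and 5. Call them X1, Y1, X2, Y2 (baseline and outcome in periods 1 and 2).

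**The plan's own figure.** n per group = 2 x SD^2 x (1 - rho) x (z_a/2 + z_b)^2 / delta^2. At 90% power: 2 x 64 x 0.5 x 10.507 / 6.25 = 107.6 per group, 215.2 in total, and x 1.2 = 258.2. So 258 is reproduced at 90% power with a 20% addition, in line with the stated power above 80%. The article gives no variance for the primary model.

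**One common slope, equal correlation 0.5** (variances in units of SD^2, sums and differences divided by root 2):
- Within patient: Var(X) = 1 - 0.5 = 0.5. The covariance of the baseline and outcome differences is 0, so the within-patient slope is 0.
- Between patients: Var(X) = 1 + 0.5 = 1.5 and the covariance is 2 x 0.5 = 1.0, so the slope is 0.67.
- The likelihood weights each part by its inverse residual variance: b = (1.0/Lb) / (1.5/Lb + 0.5/Lw), with Lb = 1.5 - 2b + 1.5b^2 and Lw = 0.5(1 + b^2). The solution is b = 0.442, with Lb = 0.909 and Lw = 0.598. Check: 1.100 / (1.650 + 0.837) = 0.442.
- Variance of the contrast relative to no baseline: 1 + 0.442^2 = 1.196.
- Standard error with 208 completers: sqrt(64/208) = 0.555 without a baseline, sqrt(64 x 1.196/208) = 0.607 with the common slope. The interval is about 9% wider (sqrt 1.196 = 1.094).

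**Simulation check** (REML, 1,500 trials, 208 completers): mean slope 0.441. Model standard errors were 0.553 (no baseline), 0.605 (one slope) and 0.554 (separate within-patient term). The variance ratio of one slope to no baseline was 1.20 model-based and 1.17 empirical.

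**Other correlation structures** (assumed; the article gives one value only):

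| Structure | Variance ratio, one slope vs no baseline |
|---|---|
| Equal, 0.3 / 0.4 | 1.07 / 1.12 |
| Equal, 0.7 | 1.44 |
| Exponential decay over months 0/2/3/5, 0.5 between outcomes | 1.21 (within-patient slope 0.15) |
| Same-period 0.60 / 0.65, across periods 0.5 | 1.10 / 1.02 |
| Same-period 0.70 / 0.80, across periods 0.5 | 0.92 / 0.68 |

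The loss becomes a gain at a same-period correlation of about 0.66. Even at 0.70 and 0.80 the one-slope model has 10% and 6% more variance than a model with its own within-patient slope.

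**Power with 208 completers.** Paired formula: 99.5% without the inflation, 98.5% with it. Reading the calculation as two groups of 104: 89.0% and 83.0%.

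**Carry-over confined to the second baseline.** Morning aspirin is taken during washout, so a residual bedtime effect c would appear in one sequence only. The shift is b x c / 2 = 0.442 x 1 / 2 = 0.22 mmHg per 1 mmHg, in the direction that enlarges the bedtime effect. Simulation with 1 mmHg: -0.21, against about 0.01 with no baseline or a separate within-patient term.

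**Season.** For a yearly sine of amplitude A and outcomes three months apart, the variance of the seasonal difference is 2 x A^2 x sin^2(pi/4) = A^2. For an assumed A of 2-3 mmHg this is 4-9 mmHg^2, or 6-14% of the within-patient difference variance of 64. With month-of-start and period terms fitted and A = 3, the simulated standard error (no baseline) was still 0.579, against 0.545 without season, with no bias.

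**Period.** For a period shift d, the within-patient bedtime-daytime difference moves by -d in one sequence and +d in the other. If period is not fitted, d cancels from the mean when the sequences are equal in size but stays in the residual variance. If completion is unequal, d x (difference in completers) / (total completers) reaches the estimate. Sequence is constant within a patient and removes neither effect.

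**The case against.** The strongest reply is that the article never says one coefficient, and that the coding of a covariate is commonly left to the full protocol or analysis plan. This stands in part: the single slope is an inference, and the size of the loss depends on it. But the article does fix a period-specific baseline in a random-intercept model, and the plain reading of that gives one coefficient.

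A reader might infer that the loss is at least 20%. The documents do not support that. One correlation is given, with no statement that it applies to every pair of ABPMs, and the loss is smaller at lower correlations and reverses at high same-period correlation. The planned patient-level covariates would also lower the common slope: if they explain 10-20% of between-patient variance (an assumption), the inflation is about 15-17%. An assumed seasonal amplitude of 3 mmHg, which the period baseline partly tracks, brings it to about 15%.

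A reader might also infer that the plan leaves within-patient time effects uncontrolled. A fitted period term does control the average shift between periods, and the planned test of whether the bedtime effect depends on period would ordinarily carry a period main effect. Only the lack of a firm commitment remains.

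Finally, carry-over is hypothetical. The plan assesses it first, and the Washout period section argues that a week should be enough, against at least 15 days allowed. The shift per mmHg shows sensitivity; it is not a prediction.

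**Conclusion.** The point holds as a matter of efficiency and wording. If the baseline enters with one coefficient and the correlation of 0.5 applies equally to all four ABPMs, the planned adjustment makes the variance of the primary contrast about 20% larger than no adjustment. It is 7-12% larger at 0.3-0.4 and about 21% larger under exponential decay. The sign changes only if same-period correlation is clearly higher than cross-period correlation, for which the article gives no evidence. In the structures examined, a separate within-patient slope did as well or better in large samples.

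Month of study start, read as each patient's own start, cannot adjust for seasonal change between the two outcome ABPMs. Under 1:1 sequences this is noise, not bias. The wording on period leaves open the omission of the one term that controls the average shift between periods.

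It would be wrong to conclude that the primary test is invalid or the trial underpowered. Without carry-over the estimate is unbiased, its standard error is valid, and power stays above 80% on either reading of the sample size calculation.

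**What to change.** State the following in the primary model before unblinding:

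1. Enter the baseline as two terms, the patient's mean baseline and the period baseline minus that mean, each with its own coefficient. Alternatively use the period-1 baseline only. That is simpler and keeps the second baseline out of the contrast, but gives up any gain if same-period correlation proves high.
2. Always include period as a fixed effect, whether or not sequence is also fitted.
3. Replace month of study start with the calendar month or season of each end-of-period ABPM.

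The cost is one extra baseline coefficient and a few season terms. No new data or visits are needed.

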### Participants

#### Inclusion criteria

To be eligible for inclusion patients will need to:

•Be aged >18 years of either sex

•Have diagnosis of hypertension

•Have treated hypertension; this is when at least the patient receives one antihypertensive drug

•Be primary care users in which anti-hypertensive drug regimen has not been changed in the last 3 months

•Have a medical history of a cardiovascular event at least 6 months previously (ischaemic heart disease, cerebrovascular accident (CVA), peripheral arterial disease) and have been treated at least for 3 months with low doses of ASA (75–125 mg)

•Sign an informed consent form

•Complete, prior to inclusion, a washout period of 1 month during which they take ASA in the morning, if they had been under regular treatment with ASA at bedtime

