#### Exclusion criteria

Patients will be excluded if they meet any of the following criteria:

•Being pregnant or breastfeeding

•Having poorly-controlled high blood pressure, defined as having a systolic BP >150 mmHg or a diastolic BP >95 mmHg in two successive health checks

•Requiring non-steroidal anti-inflammatory drugs (NSAIDs) on a daily basis

•Having a severe or terminal disease

•Being diagnosed with a physical or mental disorder that would hinder their collaboration

•Taking other antiplatelet or anticoagulant agents concomitantly

•Being on ASA at doses outside those stated in the inclusion criteria

•Being a shift worker or having a very intensive night-time work schedule

•Remaining unstable despite the treatment or requiring regular adjustments of the treatment due to their clinical status

•Being a heavy drinker, consuming >280 g of alcohol per week in the case of men or >170 g for women

•Having congestive heart failure or moderate to severe chronic renal failure that is New York Heart Association (NYHA) stage ≥III or a glomerular filtration rate < 45 mL/min

•Patients having low blood pressure ≤ 110/60 mmHg

*Withdrawal criteria*:

•Undergoing changes in their treatment within the 5-month period of the trial

•Requiring admission to hospital during the clinical trial

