In the second follow-up visit, the nurse will check patient adherence to the treatment again, by counting the empty blisters and directly asking the patients about their daily intake of the drugs, whether they took the medication at the right time and whether there had been any changes with respect to their initial medication regimen. In the event of non-adherence and/or when new drugs had been introduced, the nurse will contact the research team, to decide whether the patient should continue or be withdrawn from the study. In addition, the nurse will be in charge of investigating whether there had been adverse effects and collect the empty blister packs. In the second follow-up visit, just before completion of the first period, the blood pressure monitor will be fitted on the patient for the second 24 h of ABPM. The following day, the nurse will remove the device, make an appointment for between 15 days and 1 month later, and provide the medication for this time, which corresponds to the washout period (see below). Then the first period of the trial will have been completed (Figure 1).

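### The intention-to-treat model adjusts for medication changes that arise after randomisation, so its coefficient is in general not the intention-to-treat effect

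*Protocol article*

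**What the plan says.** The Analysis section sets the principle and the contrast: "The analysis will be carried out on an intention-to-treat basis, comparing the mean blood pressure at the end of the period of bedtime intake" with the reading after daytime intake, adjusted for blood pressure at the start of each period. It then names the model: "the 95% confidence interval will be calculated using mixed-effect models analysis of covariance for repeated measures of blood pressure", with a random intercept for the patient. For the same models, in addition to the baseline levels, it adds: "we will adjust for potential confounding or modifying variables: changes in medication, period or sequence". Age, sex, smoking, dipper status, comorbidities and calendar month of entry follow in the same list. A separate supportive analysis is defined: "we will perform a per protocol analysis with only the patients have not change in their treatment within the 5-month period of the trial", further limited to patients who were not withdrawn.

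Three other places bear on when such changes happen and what follows from them:
- Inclusion criteria: entry requires that the "anti-hypertensive drug regimen has not been changed in the last 3 months".
- Exclusion criteria, under the withdrawal criteria: "Undergoing changes in their treatment within the 5-month period of the trial".
- First period: after non-adherence or a new drug, "the nurse will contact the research team, to decide whether the patient should continue or be withdrawn from the study".

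**The concern.** In a randomised cross-over, the order of bedtime and daytime intake is set by chance. A variable that arises after allocation therefore cannot be a confounder of the contrast. It can be a consequence of treatment. If bedtime aspirin lowers blood pressure, fewer patients may need their therapy stepped up in that period. The article's Discussion accepts the general link, since it expects that lower pressure could reduce the need for antihypertensive drugs.

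Conditioning on such a variable has two effects. It takes out whatever part of the difference runs through medication. It also compares patients with and without a change, who may differ in underlying pressure. The coefficient is then not in general the effect of assigned timing, although the analysis is labelled intention to treat. At stake is what the main estimate means, and possibly some of its size.

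**Working it through.** **1. Is the covariate post-randomisation?** Entry requires a stable antihypertensive regimen over the preceding 3 months. The withdrawal criterion and the per-protocol set both refer to changes during the trial. The nurse asks about departures from the initial regimen at the second follow-up visit, when the outcome monitor is fitted. The covariate therefore records in-trial events.

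**2. Can changed patients be in the model?** The withdrawal criterion would remove them, but the visit procedure leaves continuation to a decision in each case. The Analysis section uses all available data, and only the per-protocol set excludes changed patients. So some can be present.

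**3. How far can the estimate move?** The plan states no figure to reproduce. For within-patient least squares with a period term:

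unadjusted effect = adjusted effect + γ × δ

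Here γ is the fitted medication coefficient and δ is the proportion changed under bedtime intake minus that under daytime intake. The adjusted estimate thus departs from the unadjusted one by −γ × δ. With δ negative, the sign depends on γ. The drug's own effect pushes γ down. Selection of patients with high pressure pushes it up.

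Inputs from the Sample size section: difference 2.5 mmHg, SD 8, within-patient correlation 0.5. Everything else below is assumed.

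*First set of assumptions.* A change occurs when mid-period pressure plus noise (SD 3) exceeds a threshold 5, 9 or 13 mmHg above the daytime mean, and half of the within-patient variance is shared with the end-of-period reading. Simulated with 1,000,000 patients per row:

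| Changed, daytime / bedtime | Drug lowers BP by | Unadjusted | Adjusted | γ |
|---|---|---|---|---|
| 25.4% / 16.0% | 0 | −2.49 | −1.98 | +5.48 |
| 25.5% / 16.1% | 3 | −2.23 | −2.00 | +2.48 |
| 25.4% / 16.0% | 6 | −1.94 | −1.99 | −0.53 |
| 11.6% / 6.4% | 0 | −2.49 | −2.19 | +5.72 |
| 11.6% / 6.4% | 3 | −2.34 | −2.20 | +2.65 |
| 11.7% / 6.4% | 6 | −2.18 | −2.20 | −0.29 |
| 4.3% / 2.0% | 0 | −2.50 | −2.36 | +6.12 |
| 4.2% / 2.0% | 3 | −2.44 | −2.38 | +3.05 |
| 4.3% / 2.0% | 6 | −2.38 | −2.38 | +0.05 |

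Check of row 1: δ = 0.160 − 0.254 = −0.094, and −1.978 + 5.482 × (−0.094) = −2.49. The largest movement is 0.51 mmHg toward zero, and the smallest is nil.

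*Second set of assumptions.* A change occurs when mid-period pressure is more than 8 mmHg above the mean, and the drug lowers pressure by 5 or 8 mmHg. About 21% of patients change at some time. The trigger error correlates 0 to 0.8 with the end-of-period error, and the change may or may not persist. Unadjusted estimates ran from −1.98 to −2.36 and adjusted ones from −1.99 to −2.50. Differences ran from about 0.5 mmHg larger than the unadjusted effect to 0.2 mmHg smaller. For a drug with a true effect of −5, γ ran from −5.0 to +3.7.

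The larger end can be checked by hand. The trigger is 8/8 = 1 SD away under daytime intake and 10.5/8 = 1.31 SD away under bedtime intake, which gives 15.9% and 9.5%, so δ = −0.064. With an 8 mmHg drug and no error correlation, γ = −8. The unadjusted effect is −2.5 + 8 × 0.064 = −1.99 and the adjusted effect is −2.50, a movement of 0.51 away from zero.

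**4. Scale.** With 20% losses, 258 × 0.80 = 206.4 patients are evaluable. The standard error of the paired difference is √(2 × 64 × 0.5 / 206.4) = 0.56 mmHg. A movement of 0.51 is 20% of 2.5 mmHg and about 0.9 of a standard error.

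These simulations leave out the adjustment for period baseline and are illustrations only.

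**The case against.** **The cause of changes is not stated.** A reader might infer that medication changes in this trial are driven by blood pressure. The document does not say so: the withdrawal criterion and the visit procedure refer to treatment changes and new drugs of any kind, and the Discussion remark concerns later benefit. This stands. The link is plausible and no more.

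**Changes may be rare.** Entry needs a stable regimen, poorly controlled patients and those needing regular adjustment are excluded, and a change is a ground for withdrawal. The assumed rates may be high. This stands and limits the likely harm.

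**A bias of known size or direction.** A reader might infer one from the illustrations. They do not support it: the largest movements go opposite ways, each is under one standard error, and several are near zero. Even at a true 2.0 mmHg, power is about 95% (2.0/0.557 − 1.96 = 1.63). In the hand-checked case the adjusted fit recovers the assumed direct effect of −2.5. That needs change to be unrelated to the end-of-period error, and the result is still not the intention-to-treat effect.

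**The only covariate that varies within a patient.** This too might be inferred. Dipper status is in the same list, is derived from ambulatory monitoring, and is not fixed at baseline in the Analysis text.

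**A separate baseline-only model.** The intention-to-treat sentence names only baseline adjustment, so one could read the longer list as belonging to another model. The text does not bear this out: the list is introduced as additional to the baseline levels in the models that give the effect and its interval.

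**Conclusion.** The point holds on what is estimated. The plan fixes an in-trial, post-randomisation variable as a covariate in the model for its intention-to-treat effect. That variable is not a confounder and could be affected by the assigned timing, so the coefficient is in general not the effect named. No version without the term is stated, and the adjustment is not labelled as sensitivity.

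No material bias is shown. The possible movement runs from almost nothing to about 0.5 mmHg of 2.5 mmHg, in either direction, and rests wholly on assumed change rates, triggers and drug effects. If few changed patients remain in the data, it will be small.

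**What to change.** - Remove the medication-change term from the primary intention-to-treat model.
- Keep any medication-adjusted fit as a labelled sensitivity analysis beside the existing per-protocol analysis.
- Report the number and type of medication changes under bedtime and daytime intake.
- State that every end-of-period reading available after a change enters the primary analysis.
- Reconcile three places: withdrawal on treatment change (Exclusion criteria), case-by-case continuation (First period) and intention to treat on all available data (Analysis). Which clinical rule applies is for the sponsor to settle.

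The model change is one deleted term and needs no new data. The reconciliation may cost more, because a withdrawn patient may have no later monitoring, and removing a covariate does not create the missing outcome. At submission 104 of 258 patients had been recruited and the analyst was to be blind to timing, so at that stage the change could be made without knowledge of results.
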